### Monitoring and safety

All adverse events, including serious adverse events (SAE), will be recorded and followed up for the duration of the study or until resolution. Assessment of adverse events will be performed by study investigators. All SAEs will be graded and reported to the sponsor. Any suspected unexpected serious adverse reactions will be reported to the sponsor and ethics committee.

### Sub-study- control subjects

The beneficial effects of biventricular pacing are related to the reversal of dyssynchrony. The prevalence of dyssynchrony in patients with preserved LV function awaiting cardiac surgery and the effect of bypass surgery on indices of dyssynchrony requires further evaluation.

Therefore, patients in sinus rhythm, EF ≥ 45% and awaiting revascularisation will be invited into the sub-study. A transthoracic echocardiogram will be performed (Table 5) before and after surgery, on day 3-5. The data will be analysed for acute changes in mechanical dyssynchrony after on-pump surgery.

Wang et al [25] measured the interventricular delay in hypertensive subjects with preserved LV function- 21 msec ± 19. Using a 5% significance level and 80% power, to detect a 20 msec change in IVMD, a sample size of 8 subjects is needed.

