### Statistical Analysis

No previous studies have investigated the effect of BiV pacing on the duration of level 3 care after cardiac surgery; previous studies have reported the total duration of CITU stay.

Pokushalov et al [20] reported an average CITU stay of 3.9 ± 0.6 days in the subjects after cardiac surgery, compared with 2.5 ± 0.5 days in subjects who had BiV pacing after cardiac surgery - a 36% reduction. We anticipate that the duration of level 3 care will be shorter than the duration of CITU stay, perhaps with less variance, but we have used these mean values and standard deviations for our power calculation.

Using the standard formula described by Campbell and Matchin [23]:

$$\text{Sample}\;\text{size}=\frac{2\times {\left({\text{Z}}_{1\alpha }+{\text{Z}}_{2\beta }\right)}^{2}\times \sigma^{2}}{\delta^{2}}$$

σ = standard deviation of the population

δ = anticipated benefit from the intervention

(Z_1α _+ Z_2β_) = normal distribution of function

(1-β) = 80% and α = 5%.

From standard tables (Z_1α _+ Z_2β_) ^2 ^= 7.85

$$\text{Sample}\;\text{size}=\frac{2\times \left(7.85\right)\times 0.6^{2}}{{\left(0.15\times 3.9\right)}^{2}}=\frac{5.652}{0.342}=16.5$$

In order to demonstrate a 15% reduction in the duration of level 3 care, with power 80% and with p < 0.05 for a two-sided test, the estimated total sample size required is 34 subjects.

For haemodynamic comparison of paired data at 18 hours to compare BiV pacing to standard (AAI) pacing, Hanke et al [24] observed a cardiac index of 2.7 ± 0.6 L/min/ml^2 ^in the standard pacing group. Allowing a 0.3 L/min/ml^2 ^(11%) improvement in cardiac index with BiV pacing, significance 5% and power 80%, a sample size of 32 subjects would be required.

Considering both of these previous studies, the minimum number of subjects who will be recruited and randomised into this study, will be 34; allowing for a 1/3 drop-out rate, the minimum number to be recruited will be 45. In the 2 cardiac surgical centres in which this study will be performed the proportions of all patients undergoing cardiac surgery who have impaired LV function and sinus rhythm, and who would therefore be eligible for the study are 2% and 8% (approximately 65 patients in a total of 1414 operations per year); this study should therefore be feasible within a maximum of 2 years.

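### Both paired sample sizes use a between-patient SD as the SD of within-patient change, and 8 sub-study subjects give about 72% power, not 80%, with a two-sided paired t-test if that SD is right

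*Protocol article*

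**What the plan says.** The Statistical Analysis section sizes the 18-hour cardiac index comparison, the first secondary endpoint listed, as a within-patient one: "For haemodynamic comparison of paired data at 18 hours to compare BiV pacing to standard (AAI) pacing". Its variance input is one condition of an earlier study, which "observed a cardiac index of 2.7 ± 0.6" under standard pacing. With an improvement of 0.3, it concludes that "a sample size of 32 subjects would be required". The section then sets a minimum of 34 randomised subjects, and 45 recruited to allow for drop-out.

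The section on the control sub-study plans echocardiograms "before and after surgery, on day 3-5. The data will be analysed for acute changes in mechanical dyssynchrony after on-pump surgery". Its variance input is a study that "measured the interventricular delay in hypertensive subjects with preserved LV function- 21 msec ± 19". It concludes: "Using a 5% significance level and 80% power, to detect a 20 msec change in IVMD, a sample size of 8 subjects is needed".

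Neither section gives an SD of within-patient change or a correlation between the paired measurements. The analysis text names the paired t-test for haemodynamic data. The sub-study section names no test and no sidedness. Two-sided testing is stated only for the primary endpoint.

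**The concern.** The precision of a paired comparison depends on the SD of the differences within patients. That SD can be smaller or larger than the spread of a single measurement across patients, depending on how strongly the two measurements correlate. When the single-measurement SD is put in its place without comment, the stated 80% power rests on a correlation that nobody has stated or justified.

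The sub-study has a second difficulty. A formula built on normal quantiles treats the SD as known. With 8 subjects it is estimated on 7 degrees of freedom, and the t critical value is well above 1.96. The power claimed is then not the power that a two-sided t-test delivers.

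At stake is how a null result would be read: a sub-study that finds no change in dyssynchrony, or a cardiac index comparison that finds no benefit, would be judged against a power figure that may be wrong.

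**Working it through.** **Inputs (protocol article).** Cardiac index: SD 0.6, difference 0.3, 5% significance, 80% power, stated n = 32, planned minimum 34 (Statistical Analysis). IVMD: SD 19 msec, difference 20 msec, 5% significance, 80% power, stated n = 8 (sub-study section). The multiplier 7.85 is the protocol's own value for two-sided 5% and 80% power.

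**Step 1: reproduce the stated figures.** For paired data, n = 7.85 × SD² / δ².
- Cardiac index: 7.85 × 0.36 / 0.09 = 31.4, so 32. This matches.
- IVMD: 7.85 × 361 / 400 = 7.08, so 8. This matches.

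The two-sample form (twice these values) gives 62.8 and 14.2, that is 63 and 15 per group, and does not match. So the stated figures are paired calculations with the quoted SD entered as the SD of the differences.

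**Step 2: the implied correlation.** With equal variances, SD of differences = SD × √(2(1 − ρ)). This equals SD only if 2(1 − ρ) = 1, so ρ = 0.5.

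**Step 3: sub-study power if the SD of change is 19 msec.** Noncentrality is (20/19) × √n. At n = 8 it is 1.0526 × 2.828 = 2.977, and the two-sided 5% critical value on 7 degrees of freedom is 2.365.

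| n | Normal approximation, two-sided | Paired t, two-sided | Paired t, one-sided |
|---|---|---|---|
| 7 | 79.5% | 64.4% | 79.1% |
| 8 | 84.6% | 72.4% | 84.8% |
| 9 | 88.5% | 78.9% | 89.1% |
| 10 | 91.4% | 84.1% | 92.2% |

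The two-sided paired t-test first passes 80% at n = 10.

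**Step 4: sensitivity to the correlation** (two-sided paired t; the values of ρ are assumptions, since the document gives none).

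| ρ | IVMD: SD of change (msec) | Power at n = 8 | n for 80% | Cardiac index: SD of differences | Power at n = 32 | Power at n = 34 | n for 80% |
|---|---|---|---|---|---|---|---|
| 0 | 26.9 | 44% | 17 | 0.85 | 49% | 52% | 65 |
| 0.3 | 22.5 | 58% | 12 | 0.71 | 64% | 67% | 46 |
| 0.5 | 19.0 | 72% | 10 | 0.60 | 78% | 81% | 34 |
| 0.7 | 14.7 | 91% | 7 | 0.46 | 94% | 95% | 21 |

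By the same calculation, 80% power is reached with 8 sub-study subjects at a correlation of about 0.59 or more, and with 34 cardiac index subjects at about 0.49 or more.

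**The case against.** A reader might infer that the article contains an arithmetic error, or that it breaks its own analysis plan. Neither inference is supported. Both figures follow from the normal formula that the protocol uses, and by that method 8 subjects have 84.6% power. The analysis text assigns the paired t-test to haemodynamic data, not to the echo sub-study, which names neither test nor sidedness. The 72% is therefore conditional on a two-sided paired t-test; a one-sided one would give 84.8%. Two-sided is still the natural reading, because the primary endpoint uses it and the sub-study looks for a change without stating a direction.

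A reader might also infer that both comparisons are underpowered because of the SD chosen. The documents do not show this. The error could run either way. For cardiac index, the pacing modes are compared within one study session, with at least 5 minutes after each change, so a moderate or high correlation is plausible, though no figure is given. The article also plans on at least 34 subjects rather than 32, and 34 gives 80.8% if the SD of differences is 0.6. Even at 32 the t correction alone costs under 2 points (78.2%).

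Finally, this is a condensed article about a secondary endpoint and a small non-randomised sub-study, and the full protocol may justify the SD. That limits the weight of the point. It does not remove it, because the power and size are printed as settled, with an input that is not the quantity a paired test needs.

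**Conclusion.** The point holds as a planning assumption left unstated in two places, plus a small-sample shortfall in one.

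- **Both sizes** rest on a cross-sectional SD used as the SD of change, equivalent to a correlation of 0.5. The direction of the resulting error is unknown.
- **Sub-study:** on its own SD of 19 msec, a two-sided paired t-test on 8 subjects has about 72% power. The 80% target needs 10. This rests on the test and sidedness assumed here and on normally distributed changes.
- **Cardiac index:** the weaker half. If the SD of differences is 0.6, the planned minimum of 34 meets the target. What is missing is the statement of that condition and of how far power moves if it is wrong.

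The primary endpoint calculation is not affected by this point.

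**What to change.** In the sub-study section, replace the sample size sentence with one to this effect: 8 subjects give about 72% power (10 for 80%) with a two-sided paired t-test if the SD of change is 19 msec. This also fixes the test and its sidedness.

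In the Statistical Analysis section, state that the cardiac index size assumes an SD of within-patient differences of 0.6, that is, a correlation of 0.5. Give the power at the planned minimum of 34: 81% at correlation 0.5, 67% at 0.3 and 95% at 0.7.

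The cost is two sentences. No added recruitment is required: the sub-study can keep 8 subjects with the lower power stated.

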### Summary

This trial is designed to assess the clinical and haemodynamic response to temporary BiV pacing after cardiac surgery. All subjects in sinus rhythm with severe LV systolic impairment (EF ≤ 35%) will be enrolled, irrespective of QRS duration or pre-operative requirement for intra aortic balloon counter pulsation.

A reduction in the length of level 3 care, acute haemodynamic optimisation or protection against arrhythmias or renal dysfunction/haemofiltration with BiV pacing would be a clinically significant finding.

### Trial status

The trial started recruitment in February 2009 and we have recruited 31 patients.

## List of abbreviations

AAI: Atrial inhibited pacing; APEI: Aortic pre-ejection interval; AV: Atrio-ventricular; BiV: Biventricular; BNP: Brain naturetic peptide; BPM: Beats per minute; CABG: Coronary artery bypass surgery; CCO: Continuous cardiac output; CI: Cardiac index; CITU: Cardiac intensive care unit; CRT: Cardiac resynchronisation therapy; CW: Continuous wave Doppler; DCM: Dilated cardiomyopathy; DDD: Dual chamber pacing; EC: Electrocardiogram; eGRF: Estimated glomerular filtration rate; EF: Ejection fraction; IVRT: Isovolaemic relaxation time; LA: Left atrium; LAD: Left anterior descending coronary artery; LOS: Length of stay; LV: Left ventricle; LVEDV/LVESV: Left ventricular end-diastolic volume/left ventricular end-systolic volume; MAP: Mean arterial pressure; MR: Mitral regurgitation; MVI: Myocardial velocity imaging; NGAL: Neutrophil gelatinase associated lipocalin; PA: Pulmonary artery; PPEI: Pulmonary pre-ejection interval; PW: Pulse wave Doppler; RA: Right atrium; RV: Right ventricle; RVOT: Right ventricular outflow tract; SAE: Serious adverse event; TD: Thermodilution; TnT: Troponin T; VV: Interventricular; VVI: Ventricular inhibited pacing
